#### Exclusion criteria

2.5.2

Patients with any of the following conditions will be excluded:

(1)Those who are pregnant, nursing or preparing for pregnancy(2)Those with diseases of the liver, kidney, hematopoietic system, or endocrine system, or other serious primary and mental diseases(3)Those with other spinal diseases, tumors, or cerebral infarction that affect limb sensation and function(4)Those who are participating in clinical studies of other drugs

#### Interventions

2.5.3

All patients will receive routine anti-inflammatory and analgesic treatment after surgery.

Experimental group: Patients will be given the Qishe pill (orally twice a day, 1 package (3.75 g) at a time. Control group: Methycobal will be taken orally 3 times a day, 1 tablet at a time. The course of treatment will be 12 weeks.

### Randomization and allocation

2.6

We will randomize all included patients using a table of random numbers. The 288 patients will be randomly divided into the experimental group and the control group in a 1:1 ratio according to the treatment order.

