### Study design

2.1

This is a multicenter, randomized clinical trial with 2 parallel arms (Fig. 1). We will recruit 330 patients from 2 medical institutions in Shanghai, China: Longhua Hospital Affiliated with Shanghai University of Traditional Chinese Medicine, and Long March Hospital Affiliated with Second Military Medical University. All patients will be randomly assigned to either an experimental group or a control group. Patients in the experimental group will be required to take the 3.75-g Qishe pill twice daily after breakfast and dinner, and patients in the control group will take 1 Methycobal tablet 3 times daily. All drugs will be administered orally for 12 weeks.

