#### Primary outcomes

2.7.1

The primary outcomes include the items:

JOA scores assessed the patients’ cervical spine function based on the sensation and movement of the limbs, sensation of the chest and abdomen, and bladder function. In addition, the improvement rate of JOA will be compared.^[14]^ 

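### As described, the trial is in effect open-label: a random number table is used in treatment order, and neither allocation concealment nor masked scoring of the primary JOA is described

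*Protocol article*

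**What the plan says.** **Allocation (section 2.6).** The section has two sentences. The first is "We will randomize all included patients using a table of random numbers". The second says that 288 patients will be "randomly divided into the experimental group and the control group in a 1:1 ratio according to the treatment order". Neither says who holds the list, how an assignment is released, whether blocks are used, or whether the two hospitals have separate lists.

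**Design (section 2.1).** "This is a multicenter, randomized clinical trial with 2 parallel arms". Masking is not mentioned, and the article does not call the trial open-label either. The same section states "We will recruit 330 patients from 2 medical institutions in Shanghai, China".

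**Regimens (section 2.5.3).** Experimental arm: "Patients will be given the Qishe pill (orally twice a day, 1 package (3.75 g) at a time". Control arm: "Methycobal will be taken orally 3 times a day, 1 tablet at a time". No dummy is described for either arm.

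**Primary outcome (section 2.7.1).** JOA covers "cervical spine function based on the sensation and movement of the limbs, sensation of the chest and abdomen, and bladder function", and the JOA improvement rate will also be compared. The section does not say who does the scoring. Sections 2.10 and 2.11 provide for training of investigators and a common standard of judgement, but mention no independent or masked rater.

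**The concern.** Two routes to bias are open if the trial is run as the article describes it.

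**Selection.** A list worked through in order is safe only while the people who enrol patients cannot see the next entry. If they can, they can enrol, delay or decline a patient in the light of the coming assignment, and prognosis may then differ between arms from the start.

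**Detection.** Products that differ in form and daily frequency, without a dummy, tell patients their treatment, and anyone who prescribes, dispenses or asks about intake learns it too. Once patients cannot be masked, a rater who does not know the arm is the main protection left for JOA, and none is described. Part of JOA (sensation, bladder function) depends on what the patient reports, so some exposure remains even with a masked rater.

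The sample size makes this matter more. At 132 per arm the trial is precise enough for a small systematic difference in scoring, unrelated to treatment, to become statistically significant.

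**Working it through.** **Inputs.** Section 2.4: JOA 13.68 (SD 1.83) on control and 15.65 (SD 1.61) on experimental treatment, alpha 0.05, power 90%, 132 per group, 20% loss, 330 in total. Section 2.12: two-sided testing. Assumed by us, with no anchor in the document: a systematic scoring tilt b of 0.2, 0.3 or 0.5 JOA points in favour of one arm.

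**1. The plan's own figures.**
- Pooled SD = √((1.83² + 1.61²)/2) = √2.9705 = 1.7235. Planning difference = 15.65 − 13.68 = 1.97.
- n per group = 2 × (1.96 + 1.2816)² × 2.9705 / 1.97² = 16.1, so 17. The stated 132 is not reproduced. Using the stated correlation of 0.8 as a baseline adjustment, a change score or a mean of repeated measures gives fewer still (4 to 14).
- The inflation is reproduced: 2 × 132 / (1 − 0.20) = 330.

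The origin of 132 is a separate matter. It is used below only because it is the number per arm that the plan intends to analyse.

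**2. Precision at the planned size.**
- SE = 1.7235 × √(2/132) = 0.212.
- Smallest observed difference reaching significance: 1.96 × 0.212 = 0.42 points.
- Difference detectable with 90% power: (1.96 + 1.2816) × 0.212 = 0.69 points.

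**3. Effect of a scoring tilt when the treatments do not differ.** False-positive rate = P(Z > 1.96 − b/SE) + P(Z < −1.96 − b/SE).

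| Assumed tilt b | b/SE | Two-sided false-positive rate |
|---|---|---|
| 0 | 0 | 5% |
| 0.2 | 0.94 | 0.155 + 0.002 = 16% |
| 0.3 | 1.41 | 0.293 + 0.000 = 29% |
| 0.5 | 2.36 | 0.654 + 0.000 = 65% |

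**4. The 288 in section 2.6.** The Abstract (Methods/design), section 2.1 and section 2.4 all give 330. With 20% loss, 288 × 0.8 / 2 = 115 per arm, below the stated 132. At 115 per arm SE = 1.7235 × √(2/115) = 0.227, and tilts of 0.2 and 0.5 give 14% and 59%. The point about bias therefore does not depend on which total is right.

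**5. Imbalance in numbers.** If the table is used without restriction, which section 2.6 leaves unclear, the 95% range for one arm's size among 330 is 147 to 183. Relative efficiency at 147/183 is 4 × 147 × 183 / 330² = 0.988, a loss of about 1%. Unequal arm sizes are not the problem.

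**The case against.** **The article is silent; it does not state an absence.** It condenses a fuller protocol that is not shown, and its overview figure and schedule table are missing from the text. A reader might infer that there is no concealment, no stratification and no masked scoring. The documents do not support that; they support only that none is described. This part of the objection stands and limits the wording. It does not dispose of the point, because the article does state sequential use of a number table and visibly different regimens without a dummy, and those choices make concealment and masked scoring necessary.

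**A random number table is a legitimate source of a sequence.** Any list prepared in advance can be foreseen by whoever holds it, so the defect exists only if recruiting staff have access. The article does not say who has access. Selection bias is therefore a possibility left open, not something shown.

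**Who scores JOA is not stated.** It is tempting to call the outcome assessor-scored and the assessors unmasked. Both are inferences from the content of the scale and from the training provisions for investigators. Different regimens show that patients will know their arm; they do not show that raters will. If patients report part of JOA themselves, however, the exposure moves to them and does not go away.

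**The tilts are assumed.** They are 10% to 25% of the planning difference (0.2/1.97 and 0.5/1.97), and 0.2 and 0.3 lie below the 0.42 points needed for significance. All are below the 0.69 points detectable with 90% power. The table in the working shows how sensitive the test is; it does not predict what will happen in this trial.

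**Stratification is a different matter.** A reader might count unstratified allocation as a source of bias. It affects balance and precision, and the cost of unequal arm sizes is about 1%. Stratifying by anterior or posterior surgery would be a preference; nothing in the article makes it necessary.

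**Conclusion.** The concern holds in a limited form. As described, the trial is in effect open-label for patients, and the article describes nothing that protects the next assignment from being foreseen or the JOA score from knowledge of the arm. At 132 per arm, an assumed tilt of 0.2 to 0.5 points would lift the false-positive rate from 5% to between 16% and 65%.

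This rests on three assumptions: the SDs quoted in section 2.4 apply, the number analysed is 132 per arm, and a tilt of that size occurs. The first two are the plan's own; the third is ours. The verdict does not say that recruiters will see the list, that raters will know the arm, or that the full protocol lacks these safeguards. It says that a primary result obtained by the method as written could not be defended against either bias. The difference between 288 and 330 is a plain contradiction and needs correction in any case.

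**What to change.** 1. **Allocation.** The coordinating hospital, which section 2.10 already makes responsible for quality control, generates a blocked list with varying block sizes, stratified by centre. The stratification is for balance and precision. Each assignment is released, by sealed opaque envelope or telephone, only after consent and baseline data are recorded.
2. **Scoring.** JOA is scored by existing trained investigators who neither prescribe nor dispense and who are kept unaware of arm. MRI is measured on de-identified images with the arm hidden.
3. **Reporting.** The conclusions name VAS, NDI and the patient-reported JOA items (sensation, bladder) as unmasked, since a masked rater does not protect them.
4. **Text.** Section 2.6 states one number of patients, reconciled with the 330 in the Abstract and sections 2.1 and 2.4.

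The cost is preparing the list and its release, a duty rota among existing staff, and image de-identification. The rota assumes that each hospital has trained staff free of prescribing and dispensing; the article does not confirm this, so it should be checked before the start. If the full protocol already contains items 1 and 2, a sentence on each in section 2.6 and section 2.7 is enough.

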**Methods/design::**

A multicenter, randomized controlled clinical trial will be conducted to evaluate the efficacy and safety of the Qishe Pill. A total of 330 patients with CSM who receive surgical treatment will be randomly divided into 2 groups, treated for 12 weeks and with a 1-year follow-up. The primary outcome will be Japanese Orthopaedic Association score from the baseline to 4 weeks, 12 weeks, 24 weeks, and 48 weeks after surgery. Secondary outcomes will include Visual Analogue Scale score, Neck Disability Index, and imaging indicators (including magnetic resonance imaging and X-ray). Additionally, adverse reactions will be observed and recorded as safety indicators.

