### Sample size calculation

2.4

On the basis of the comparison treatment, we calculated the sample size of the 2 groups (Qishe pill versus Methycobal), which will be randomly distributed in an equal manner. Since Japanese Orthopaedic Association (JOA) scores can include sensory and motor function of the limbs and bladder, we chose JOA scores to calculate the sample size with an estimated correlation coefficient of the measurements of ρ=0.8 and with an alpha = 0.05. The JOA score was 13.68 ± 1.83 at the 6-month follow-up after oral administration of Methycobal, and 15.65 ± 1.61 at the 6-month follow-up after oral administration of traditional Chinese medicine for promoting blood circulation and removing blood stasis, so the calculated sample size of each group is 132. Considering a 20% loss to follow-up, the total sample size needed to detect this difference at a 5% level of significance with a power of 90% is 330 patients.

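### The randomisation section allocates 288 patients, but the abstract, the design section and the sample size calculation all give 330, and nothing reconciles the two.

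*Protocol article*

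**What the plan says.** The protocol article gives the size of the trial in four places.

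- Abstract, Methods/design: "A total of 330 patients with CSM who receive surgical treatment will be randomly divided into 2 groups".
- Section 2.1, Study design: "We will recruit 330 patients from 2 medical institutions in Shanghai, China".
- Section 2.4, Sample size calculation: the groups are equal ("which will be randomly distributed in an equal manner"), "so the calculated sample size of each group is 132", and the inflation step begins "Considering a 20% loss to follow-up". The total required "at a 5% level of significance with a power of 90% is 330 patients".
- Section 2.6, Randomization and allocation: "We will randomize all included patients using a table of random numbers", followed directly by "The 288 patients will be randomly divided into the experimental group and the control group in a 1:1 ratio according to the treatment order".

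Three places therefore say 330 and one says 288. The article does not mention a run-in, a second randomisation stage or a subset that would account for 288.

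**The concern.** The abstract and section 2.6 describe the same act, the random division of patients into two groups, with totals that differ by 42. Both cannot be followed. Section 2.6 is the section someone would consult when preparing the allocation sequence, so an error there matters more than one in background text.

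Two things are at stake. If the sequence were prepared for 288, it would either have to be extended for the remaining 42 patients or randomisation would end short of the planned number. In addition, a reader of the results could not tell whether a trial that randomised 288 had been completed as planned or had stopped early.

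**Working it through.** **Inputs.** From section 2.4: 132 per group, 20% loss, 1:1 allocation, total 330, 90% power at the 5% level. The test is two-sided (section 2.12). From section 2.6: 288 patients, 1:1.

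**1. Reproduce the plan's total.** Required per group = n/(1 − loss) = 132/(1 − 0.20) = 165, and 2 × 165 = 330. This matches section 2.4 exactly.

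**2. Can 288 come from the same inputs?** The common incorrect inflation, n × (1 + loss), gives 132 × 1.20 = 158.4, rounded up to 159 per group, or 318 in total. Neither formula gives 288.

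**3. Shortfall if 288 is followed.**
- Randomised: 330 − 288 = 42 fewer, or 21 per group (144 against 165).
- Evaluable after 20% loss: 144 × 0.80 = 115.2 per group, against 132.
- Difference: 132 − 115.2 = 16.8, about 17 per group, or 16.8/132 = 12.7% fewer.
- In total: 288 × 0.80 = 230.4, against 264.

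**4. Loss that 288 could absorb.** To keep 132 of 144 per group, loss must not exceed 1 − 132/144 = 8.3%. The protocol assumes 20%.

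**5. Does this translate into lost power?** That depends on which effect is used.
- If 132 per group is taken to give 90% power, the implied standardised difference is √(2/132) × (1.960 + 1.282) ≈ 0.40. At that difference, 115 per group gives about 86%. The value 0.40 is back-calculated and appears nowhere in the protocol.
- The JOA figures actually stated are 13.68 ± 1.83 and 15.65 ± 1.61. The difference is 1.97, the pooled SD is √((1.83² + 1.61²)/2) = 1.72, and the standardised difference is 1.97/1.72 ≈ 1.14. The sample size per group for 90% power, two-sided 5%, is 2 × (1.72 × 3.242/1.97)² ≈ 16.1, that is 17. On these inputs, power is above 99.9% at both 115 and 132 per group.

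The count is therefore missed in either case, but the stated inputs do not support a statement that power falls.

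**The case against.** The best defence is that the intended number is not in real doubt. Section 2.6 opens by saying that every included patient is randomised, three other places give 330, and the inflation arithmetic reproduces 330 exactly. On this view 288 is a leftover figure and no evidence that the trial will end at 288. This is a plausible explanation and it makes the repair easy. It does not remove the contradiction from the section that governs allocation.

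A reader might infer more than the document supports, in three ways.

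- *That the planned number is lost whatever happens.* It is not. Extending the sequence to 330 gives 165 per group and 132 after 20% loss, although by a step that section 2.6 does not describe. Only stopping at 288 misses the plan.
- *That power drops from 90% to about 86%.* That figure is conditional on a standardised difference of 0.40 inferred from the 132. The stated JOA means and SDs imply 1.14, at which power is above 99.9% either way.
- *That balance between the two hospitals, or custody of the allocation list, is deficient.* Section 2.6 does not say whether one sequence serves both hospitals, and a condensed article commonly leaves blocking, stratification and list handling to the full protocol. Their absence here is no finding and has no bearing on 288 against 330.

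**Conclusion.** The inconsistency is real: 288 in section 2.6 contradicts 330 in the abstract, section 2.1 and section 2.4, and the protocol's own arithmetic supports 330. If 288 were followed and the assumed 20% loss occurred, about 115 per group would be evaluable, 17 below the planned 132. The planned count would be kept only with a loss of 8.3% or less.

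This conclusion rests on two inputs taken from section 2.4 as given: the 132 per group and the 20% loss. It concerns the planned count only. The 132 does not follow from the stated JOA means and SDs under a standard two-group comparison, which needs about 17 per group. That is a separate issue in section 2.4 and should be dealt with there; it does not reconcile 288 with 330. The document also does not establish that a list of 288 entries was actually prepared.

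**What to change.** In section 2.6, replace 288 with 330 and state the split as 165:165, in agreement with the abstract and sections 2.1 and 2.4. Confirm that the allocation sequence in use covers all 330 patients. If it was prepared for 288, record how and when it was extended.

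The cost is one corrected number and one check of the sequence. No other section has to change for this point.

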### Outcomes

2.7

#### Primary outcomes

2.7.1

The primary outcomes include the items:

JOA scores assessed the patients’ cervical spine function based on the sensation and movement of the limbs, sensation of the chest and abdomen, and bladder function. In addition, the improvement rate of JOA will be compared.^[14]^ 

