#### Inclusion criteria

2.5.1

Participants will be included if they fulfill the following conditions:

(1)Satisfy the diagnostic criteria of CSM, and have definite spinal cord compression on MRI of cervical vertebrae^[13]^(2)Aged 18 to 80 years(3)Will be receiving surgical treatment (including anterior and posterior)(4)Sign informed consent

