### Data collection and monitoring

2.10

The duration of the intervention will be 12 weeks, and follow-up will be 36 weeks. Study visits will take place at baseline and at 4, 12, 24, and 48 weeks. Every patient will be asked to visit within 3 days of the given time point. Longhua Hospital affiliated with Shanghai University of Traditional Chinese Medicine (http://www.longhua.net/ywsy/gzlc/287.jhtml) will be responsible for quality control and training for investigators.

Epidata (version 3.0) will be used to restrict data values. Two trained investigators will enter and compare the data independently to rule out the differences.

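### The JOA improvement rate is compared as a primary outcome beside the JOA score; in its usual form it can be undefined or unstable near the scale maximum, and the baseline-adjusted score would serve better alone

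*Protocol article*

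**What the plan says.** Section 2.7.1 (Primary outcomes) describes the JOA score and then says: "In addition, the improvement rate of JOA will be compared". It gives no formula and no scale maximum, and cites a reference. The abstract is narrower: "The primary outcome will be Japanese Orthopaedic Association score from the baseline to 4 weeks, 12 weeks, 24 weeks, and 48 weeks after surgery". The improvement rate does not appear there, and section 2.4 sizes the trial on the score.

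On entry, section 2.5.1 requires: "Satisfy the diagnostic criteria of CSM, and have definite spinal cord compression on MRI of cervical vertebrae". It also requires an age of 18 to 80, planned surgery and consent. Neither section 2.5.1 nor section 2.5.2 sets a JOA limit.

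Section 2.10 says: "Study visits will take place at baseline and at 4, 12, 24, and 48 weeks". Whether baseline JOA is taken before or after surgery is not stated, and no baseline mean or SD is given. Section 2.12 plans a t-test for normally distributed continuous variables and a rank sum test for the others. Neither adjusts for baseline.

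**The concern.** A ratio with (maximum − baseline) as denominator behaves badly when baseline is high. At the maximum it has no value, so those patients, who are the mildest, leave the comparison. Just below the maximum, one point up or down becomes a very large percentage, and a few such patients can carry much of the variance. Nothing at entry keeps these patients out.

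The rate and the score can also give different answers. With both under the primary heading, the article does not say which one decides. What is at stake is a primary comparison that may lose a selected subset and may conflict with the outcome named in the abstract.

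**Working it through.** **The plan's own figure.** There is none for the rate. The nearest is 132 per group on the JOA score. For the control treatment, section 2.4 uses: "The JOA score was 13.68 ± 1.83 at the 6-month follow-up after oral administration of Methycobal". For the Chinese-medicine comparator it uses a mean of 15.65 with SD 1.61 at the same time point.
- Difference: 15.65 − 13.68 = 1.97. Common SD: √((1.83² + 1.61²)/2) = 1.72.
- n per group at two-sided 5% and 90% power: 2 × (1.96 + 1.28)² × 1.72²/1.97² ≈ 16.1, so 17. The stated 132 is not reproduced; that is a separate matter.
- The dropout step does reproduce: 264/0.8 = 330.
- With 132 per group, the difference detectable at 90% power is 1.72 × √(2/132) × (1.96 + 1.28) ≈ 0.69. I therefore use an effect of 0.7 points below.

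**Assumptions not in the document.** Rate = (follow-up − baseline)/(17 − baseline); maximum 17; the baseline distributions; the 0.7-point effect; the correlation of 0.5. The correlation of 0.8 is in section 2.4, which does not say which measurements it relates.

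**Weight of one point,** 1/(17 − baseline): 11% at baseline 8, 14% at 10, 33% at 14, 50% at 15, 100% at 16, undefined at 17.

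**Share undefined.** For whole-number scores this is P(baseline ≥ 16.5) = 1 − Φ((16.5 − mean)/SD), shown with the number among 264 patients.

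| Baseline mean (SD) | Undefined | Of 264 |
|---|---|---|
| 9 (2.5) | 0.1% | 0.4 |
| 10 (2.5) | 0.5% | 1.2 |
| 11 (2.5) | 1.4% | 3.7 |
| 12 (2.5) | 3.6% | 9.5 |
| 13.68 (1.83) | 6.2% | 16.3 |

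The share depends on the SD as well as the mean: a mean of 13 with SD 2.5 gives 8.1%, about 21 patients.

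**Leverage.** Patients with a defined rate and a baseline of 15 or 16 are about 3% of the sample at mean 10 and carry about 15–27% of the rate's variance. At mean 12 they are about 13% of the sample and at mean 13.68 about 28%; there they carry 54–73%.

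**Simulation.** 132 per group; follow-up means 13.68 and 14.38, SD 1.83; scores rounded and capped at 17; undefined rates left out; 1,500 replicates. The first four result columns are power in percent. The last is the percentage of trials in which t-tests on the raw score and on the rate differ on significance.

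| Baseline mean (SD) | Correlation | Raw score, t | Rate, t | Rate, rank sum | Score adjusted for baseline | Differ |
|---|---|---|---|---|---|---|
| 10 (2.5) | 0.5 | 87 | 84 | 91 | 94 | 15 |
| 12 (2.5) | 0.5 | 85 | 70 | 85 | 92 | 26 |
| 13.68 (1.83) | 0.5 | 86 | 73 | 86 | 94 | 25 |
| 10 (2.5) | 0.8 | 85 | 99 | >99 | >99 | 14 |
| 12 (2.5) | 0.8 | 86 | 98 | 99 | >99 | 14 |
| 13.68 (1.83) | 0.8 | 86 | 97 | 99 | >99 | 14 |

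Allowing for a simulation error of up to about 2 points, the disagreement is about 12–26%. At correlation 0.8 it arises mainly because the rate uses baseline and the raw score does not, rather than from the ceiling. If the rate is tested by rank sum, the disagreement with the raw-score t-test is 11–16%.

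**The case against.** The case against is substantial. The formula, the maximum and the baseline distribution all come from outside the document, and an article may leave a formula and a handling rule to the full protocol or SAP. This stands: the absence of a formula is not the point, and everything about the ceiling is conditional. Change divided by baseline would have no such difficulty.

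A reader might infer from the 6-month means of 13.68 and 15.65 that the ceiling is active at entry. The document does not support this. Those are follow-up scores, and under the assumed form only a high baseline makes the ratio unstable. If baseline is preoperative, patients selected for surgery are less likely to be near the maximum, and at means of 9–10 about one patient in 264 or fewer is affected. If it is postoperative, more would be.

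A reader might also infer that the rate loses power in general. It does not. At the plan's own correlation of 0.8 it clearly beats the raw score. At 0.5 the loss appears mainly with the t-test, whereas section 2.12 assigns non-normal data to the rank sum test, which recovers most of it.

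Two things survive. Ranking cannot supply a value for an undefined rate, and neither test says which measure counts when they disagree. An SAP could add a formula and a handling rule, but would not ordinarily demote an outcome that the protocol lists as primary.

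**Conclusion.** The point holds in a conditional form. The document itself establishes that the improvement rate is compared under the primary outcomes, that the abstract names only the score, that entry sets no JOA limit, and that the planned comparisons ignore baseline.

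That the rate is undefined or unstable near the maximum depends on the usual recovery form. The effect is then negligible at baseline means of 9–10 and material from about 12 upwards. It cannot be said from the article that a few patients will dominate the comparison.

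The recommendation depends less on these assumptions than the ceiling problem does. The baseline-adjusted score has no undefined values, agrees with the abstract, and had at least as much power as the raw score and the rate, by either test, in every setting simulated.

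**What to change.** In section 2.7.1, make the JOA score the sole primary JOA measure. In section 2.12, state that it is analysed with baseline JOA as a covariate. Move the improvement rate to the secondary or descriptive measures, reported as median and quartiles, and count the patients at the maximum in each group. State the formula and whether baseline is before or after surgery when the rate is reported.

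This takes a few sentences and no new data. The downside is that a rate familiar to readers is no longer a primary result.
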